### Assignment of interventions: allocation

Allocation of an household to a specific study arm will follow a predefined computer-generated randomization list. The list will be generated at the central level by the pharmacist of the CRUN. The randomization list will comprise a sequence of random numbers with corresponding study arm which will be sealed in an envelope. The envelope will only be opened by field workers after enrolment of the participating household. No blinding will be applied, making the study will be an open label trial.

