### Sample size calculation

The aim of this study is to demonstrate that SMC for children between aged 3–59 months associated with the screening household members (through standard HRP2 RDT) and treatment if proven positive is superior to SMC alone in reducing the incidence of clinical malaria after 1 year. In this superiority trial the sample size is calculated to attain sufficient power to determine independently the relevant difference in malaria incidence rate between the control and the intervention arms, using classic RDT. The sample size estimation is performed under the assumption that the average number of malaria episodes per child aged between 3 and 59 months per year since the implementation of SMC in Nanoro health district varied between 1.38 and 1.76 [17–19]. Sample size of 236 in each arm will give at least 80% power to detect a 20% decrease in incidence of malaria after 1 year in comparison to a baseline incidence rate in the control arm (SMC) between 1.5–2.0 malaria cases per year, assuming a one-sided test with significance level of 0.025 and large samples z-test of the Poisson event rate difference (PASS software). To account for 10% study drop-out rate for any reason, the sample size will increase to 263 in each arm. Therefore, the final estimated sample size for this study is 526 households, with at least one child aged between 3 and 35 months to allow a follow up of the children during the study period and while benefiting of SMC. One child from each household (primary participants) will be included in the primary analysis, assuming that each household will have an average of 2 children under SMC coverage, about 1052 children under SMC coverage are expected [11]. The expected number of household members is estimated at about 1315 (263 × 5) under the assumption that each household from the intervention arm will have an average of 5 members. Data will be analysed with R software using the appropriate tests depending on the variables. Adherence to treatment and acceptability of the strategy (focus group discussion) will be assessed qualitatively.

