### Data collection

The proposed study includes two major interventions: the already existing and funded SMC intervention by the National Malaria Control Program and the newly proposed intervention (Household members screening and treatment) expected to boost the impact of the SMC intervention. For SMC intervention, complete dose (3 days regimen) of Amodiaquine + sulfadoxine-pyrimethamine will be administered monthly over a period of four months. Each monthly administration will be performed according to children age as follow: [3–11] months, SP: 262,5 mg/AQ: 76,5 mg on day 0, SP: 0 mg/AQ: 76,5 mg on day 1, SP: 0 mg/AQ: 76,5 mg on day 2, [12–59] months, SP: 525 mg/AQ: 153 mg on day 0, SP: 0 mg/AQ: 153 mg on day 1, SP: 0 mg/AQ: 153 mg on day 2. Administration of the fisrt dose will be supervised by the community health workers while the second and third doses will be administered under supervision of the study field workers. Household members screening for malaria and treatment with the combination of dihydroartemisinin-piperaquine (DHA-PPQ), is a study-specific intervention which will be implemented in parallel with SMC over the four months SMC period. Household members with positive RDT test will be treated with single daily dose of DHAPPQ over three days in accordance with the national guideline for malaria cases management as follow: [5–8[Kg, DHA 20 mg/ PPQ 160 mg, one tablet/day, [8–11[Kg, DHA 20 mg/ PPQ 160 mg, 1 + 1/2 tablet /day, [11–17[Kg, DHA 40 mg/ PPQ 320 mg, one tablet/day, [17–25[Kg, DHA 40 mg/ PPQ 320 mg, 1 + 1/2 tablet /day and for [25–36[Kg, [36–60[Kg,, [60–80[Kg and ≥ 80 Kg, DHA 40 mg/ PPQ 320 mg, two, three, four and five tablets/day respectively. Enrolled children in both control and intervention arms will be followed for 24 months to fully cover two consecutive malaria transmission seasons, including two SMC cycles, and two dry seasons. However, the superiority will be measured over one season of intervention. The analysis will be repeated on year 2 to look at similar impact with potentially a difference in transmission. Then a pooled analysis of 2 years intervention will be conducted. Children will be actively followed-up with monthly visits during each of the two malaria transmission seasons (July–December). At each visit, physical examination will be performed and anthropometric parameters will be recorded, including weight, height, and Mid-Upper Arm Circumference (MUAC). Weight will be measured with SECA 874 scale (SECA company ltd., Germany). SHAKIR strips will be used for MUAC measurement. Blood smears will be collected by finger prick for hemoglobin (Hb) measurement, malaria Rapid Diagnostic Test (RDT), microscopy and additional drop of blood will also be spotted onto filter paper for later PCR analyses. In SMC+ screening and treatement of household members with standard RDT study arm, SD Bioline Malaria Ag P.f (HRP2/pLDH), (Standard Diagnostics, Inc., Korea) will be used. A HemoCue® 201+ will be used for photometric measurement of Hb in g/dL in the field. Thick and thin blood films will be stained with Giemsa 3% for 30 min and examined with light microscope Olympus CX23. Malaria slides will be double-read by two independent microscopists. In case of discrepencies a third reader will intervein and the arithmetic mean of the two nearest densities will be considered as final results. A smear will be declared negative if the examination of 100 thick-film fields does not reveal the presence of asexual parasites. The later PCR analyses will be the genotyping malaria-positive blood samples for amodiaquine resistance molecular markers in *pfcrt* and *pfmdr1*, sulfadoxine resistance marker in *pfdhps*, pyrimethamine resistance marker in *pfdhfr*, piperaquine resistance marker on Plasmepsin 2–3 and artemisinin resistance markers in the propeller domain of the Kelch 13 (K13) gene on malaria-positive samples. Samples will be genotyped using established protocols to detect molecular markers of antimalarial drug resistance. Briefly, DNA extracted from the dried blood spots will be used as the template for amplification by polymerase chain reaction (PCR). To detect nucleotide sequence polymorphisms, cleaned PCR products will be sent to a commercial service for Sanger sequencing. Single-nucleotide polymorphisms (SNPs) will be called by comparison with the reference sequences using validated bioinformatics workflows. Gene copy number amplifications will be detected using previously published protocols [20]. Children presenting any infection other than malaria will be diagnosed and treated appropriately according to national standard of care practices. After the malaria transmission season, the follow-up will be passive during the dry seasons (January–June). Parents / guardians of the enrolled children will be asked to contact the research team based at the peripheral health facilities of the study area in case their child is unwell. During these visits, children will be diagnosed and treated according to national standard of care practices. Nevertheless, all children will be actively seen on month 24 for a study end visit. Table 1 summarises the activites for the participant assessment and follow-up troughout the study (Table 1).

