### Outcomes

The primary outcome is the incidence of clinical malaria evaluated within each year of the study in primary study participants i.e. children under SMC coverage. Secondary outcomes include (i) RDT and microscopy positivity rate from the beginning to the end of the follow-up, (ii) tolerance and safety i.e. the risk of adverse events (AEs) and serious adverse events (SAEs) after SMC drug uptake (AQSP) and after treatment with DHA-PPQ for household members (iii) prevalence of mutant alleles of *pfcrt*, *pfmdr1*, *pfdhfr*, and *pfdhps*, *plasmepsin*, and *K13* in malaria positive samples from the enrolment to the end of the follow-up periods, and (iv) adherence, (v) cost-effectiveness, and (vi) acceptability of the intervention which will be assessed qualitatively.

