## Discussion

In Sahel countries, with high seasonal malaria transmission, SMC is an important strategy for reducing malaria burden. Despite the implementation of SMC intervention as a complement to multiple other malaria control measures, such as mass distribution of LLIN, malaria burden remains high in the most vulnerable groups including children younger than five years suggesting that the expected impact of this promising intervention is not reached. In order to achieve global malaria target by horizon 2030, development of innovative strategies to improve the efficacy of these existing malaria control measure is essential. This study aims to assess the impact of an improved SMC strategy adding roommates malaria screening and treatment with DHA-PPQ if positive. If confirmed to be beneficial, this strategy will contribute to breaking the cycle of continuous infection of children from parents and older siblings, as household members are not yet targeted by any specific intervention.

The choice for DHA-PPQ is driven by several reasons including its adoption as first line treatment for uncomplicated malaria in Burkina Faso [2, 21], its longer post-treatment prophylactic effect and most importantly its proven efficacy and safety in the area [22, 23].

Microscopy will be used in addition to RDT for the detection of malaria cases and asymptomatic parasitaemia in order mitigate the issue of false positive RDT due to the persistence of HRP2 antigen after a successful malaria treatment. Furthermore, microscopy will allow a better characterization of the detected cases in terms of parasitaemia, parasite species as well as gametocyte carriage which is critical for the transmission in the area.

SMC is delivered as a prevention measure during each malaria season but in this study the follow-up period is extended up to 24 months in order to cover two consecutive malaria seasons. The rationale for this extension include increasing the power to detect rare study outcomes such as severe malaria, related-mortality, rare safety signals with special interest to known severe reactions to SMC drugs and to DHAPPQ and to have an overview of the impact of the intervention overtime.

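### The blanket no-blinding statement leaves slide readers and genotyping staff unmasked, although coding their samples would cost little

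*Protocol article*

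**What the plan says.** The allocation section rules out masking in one sentence: "No blinding will be applied, making the study will be an open label trial". In the same section, field workers open the allocation envelope once the household is enrolled, so the staff in contact with families know the arm.

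Data collection describes careful microscopy. "Malaria slides will be double-read by two independent microscopists", a third reader is called in for discrepancies, and the final density is the mean of the two nearest values. It does not say that any reader is masked to study arm. Genotyping is done later on dried blood spots, with sequencing by a commercial service. Again nothing is said about masking.

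On the outcome, the article says "The primary outcome is the incidence of clinical malaria evaluated within each year of the study in primary study participants". A secondary outcome is the "RDT and microscopy positivity rate from the beginning to the end of the follow-up". The Sample size section refers to "the relevant difference in malaria incidence rate between the control and the intervention arms, using classic RDT". The Discussion states "Microscopy will be used in addition to RDT for the detection of malaria cases and asymptomatic parasitaemia", in order to "mitigate the issue of false positive RDT due to the persistence of HRP2 antigen after a successful malaria treatment".

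Table 1 marks blood sampling at each active month, in months 19 to 23 and at month 24, but not in months 7 to 12. Case finding in the dry season is passive: "Parents / guardians of the enrolled children will be asked to contact the research team based at the peripheral health facilities of the study area".

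**The concern.** Open-label delivery is not the fault here; it follows from the nature of the intervention. The difficulty is that the sentence covers everyone, including people who never meet the family. Two readers who are independent of each other may both know the arm. Reading a low-density film, or deciding that a field holds no asexual parasites, involves judgement, and knowledge of the arm can shift it. The same holds, to a lesser degree, for genotype calls, which feed a secondary outcome.

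Masking matters more because the article itself gives microscopy the task of correcting false positives from the rapid test. A corrective reading is worth most when it is the one measurement made without knowledge of the arm. At stake is an easily gained safeguard for the microscopy and resistance-marker results. It is not the validity of the whole trial.

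**Working it through.** **1. Who can be masked, from the article's own procedures.**
- Families: no. They know whether household members are screened.
- Field workers: no. They open the envelope and work with the households.
- First, second and third slide readers: yes. They read Giemsa-stained films at a microscope, and a coded label is enough.
- Genotyping staff: yes. They work from dried blood spots by amplification and sequencing, partly outside the research unit.

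The samples and the repeated readings are already planned, so only the label changes.

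**2. The plan's sample size.** Inputs from the Sample size section: control rate 1.5 per child-year (lower end of 1.5 to 2.0), 20% reduction, one-sided 0.025, 80% power, Poisson rate difference.

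n = (z₀.₉₇₅ + z₀.₈₀)² × (λ₁ + λ₂) / (λ₁ − λ₂)² = 7.849 × (1.5 + 1.2) / 0.3² = 235.5, so 236 per arm. For drop-out, 236 / 0.9 = 262.2, so 263. Both figures agree with the plan. Masking does not change them.

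**3. Can a power loss from false-positive rapid tests be stated?** Power = Φ[(λ₁ − λ₂) / √((λ₁ + λ₂)/236) − 1.960]. The article gives no false-positive rate, so every case below is an assumption, with a true rate ratio of 0.80.

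| Assumption | Observed rates | Observed ratio | Power |
|---|---|---|---|
| No false positives | 1.50 v 1.20 | 0.80 | 80% |
| False positives proportional to true episodes, total control rate 1.5 | 1.50 v 1.20 | 0.80 | 80% |
| 0.15 per year added equally to a true 1.5 | 1.65 v 1.35 | 0.818 | 76% |
| 0.45 per year added equally to a true 1.5 | 1.95 v 1.65 | 0.846 | 68% |
| 10% of a total of 1.5 false, equal number in both arms | 1.50 v 1.23 | 0.82 | 71% |
| 30% of a total of 1.5 false, equal number in both arms | 1.50 v 1.29 | 0.86 | 49% |

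In the last two rows, a perfect microscopy endpoint would count only true episodes. These are 1.35 v 1.08 (power 76%) and 1.05 v 0.84 (power 65%). Even there, the gain from microscopy is about 5 and 16 percentage points, not the full distance to 80%. The result therefore runs from no loss to a large one, depending on figures that the article does not give.

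**4. Observer bias, for scale only.** Suppose there is no true effect, the control rate is 1.5, and knowledge of the arm lowers recorded episodes in the intervention arm by a fraction d. The chance of a false superiority result is then 4.5% for d = 2%, 9.9% for d = 5% and 27.6% for d = 10%, against a nominal 2.5%. This d covers all sources: presentation, clinical judgement and test reading. Masked reading removes only the last, and the article does not say how large that share is.

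**5. Coverage of slides.** Outcomes evaluates incidence within each year, whereas Data collection measures superiority over one season. If the full year counts, sick visits in months 7 to 12 enter the outcome, yet Table 1 marks no blood sample there. An endpoint that requires a positive slide could lose them without anyone noticing.

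**The case against.** The strongest reply is that the antigen problem is already handled. The Discussion adds microscopy for that very purpose, and Data collection sets out double reading, a third reader and a criterion for a negative smear. What is left is how to count a child who is positive on the rapid test and negative on the slide. A journal article may leave that case-definition detail to the full protocol or the analysis plan. This stands, and the absence of such a rule is not held against the article.

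A reader might also infer that the article contradicts itself, with an endpoint based on the rapid test in the Sample size section and one based on microscopy in the Discussion. The text does not support this. The mention of the classic rapid test can equally name the household screening test that defines the intervention arm, as the sentences around it do.

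Finally, masked slides cannot correct the choice of who presents or who is judged ill, which may be the larger open-label risk. This also stands. It limits what the change achieves, but it is no reason to leave the readings unmasked.

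**Conclusion.** The point holds as a cheap improvement of minor severity. The article's wording excludes masking of staff who could be masked at little cost, and no other section makes an exception for them.

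Its size cannot be given as a number. It is tempting to infer that power falls to between 71% and 49%. Those figures are arithmetically right, but they require the same absolute number of false positives in both arms and a control rate of 1.5 that already includes them. The mechanism that the article names, antigen persisting after treatment, would make false positives follow treated episodes. If they are proportional to true episodes, the ratio is not diluted at all. The observer-bias figures likewise rest on an assumed d and overstate what masked reading alone can remove.

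The conclusion assumes that slides and filter papers can be coded before they reach the readers. Nothing in the article suggests otherwise.

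**What to change.** Replace the sentence on blinding by: *Participants and field staff are not masked; all slide readers and genotyping staff receive coded samples and are masked to study arm and household.*

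Report the incidence of clinical malaria confirmed by the masked final slide reading alongside any count based on the rapid test, wherever a slide was taken. Fix which of the two is primary before outcome data are seen by arm. The article requires the analysis plan only before database lock, which in an open-label trial may be too late for that choice. State how sick visits without a slide are counted, in particular those in months 7 to 12, so that a definition based on slides alone does not drop them unseen. State as a limitation that masked reading does not protect against differences in who presents or is judged symptomatic.

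The cost is the coding of sample labels, a key held away from the readers, and a few sentences of text. The change concerns only how samples are read and episodes are counted. The sample size is unaffected, provided that its control rate refers to the endpoint chosen as primary.

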### Data collection

The proposed study includes two major interventions: the already existing and funded SMC intervention by the National Malaria Control Program and the newly proposed intervention (Household members screening and treatment) expected to boost the impact of the SMC intervention. For SMC intervention, complete dose (3 days regimen) of Amodiaquine + sulfadoxine-pyrimethamine will be administered monthly over a period of four months. Each monthly administration will be performed according to children age as follow: [3–11] months, SP: 262,5 mg/AQ: 76,5 mg on day 0, SP: 0 mg/AQ: 76,5 mg on day 1, SP: 0 mg/AQ: 76,5 mg on day 2, [12–59] months, SP: 525 mg/AQ: 153 mg on day 0, SP: 0 mg/AQ: 153 mg on day 1, SP: 0 mg/AQ: 153 mg on day 2. Administration of the fisrt dose will be supervised by the community health workers while the second and third doses will be administered under supervision of the study field workers. Household members screening for malaria and treatment with the combination of dihydroartemisinin-piperaquine (DHA-PPQ), is a study-specific intervention which will be implemented in parallel with SMC over the four months SMC period. Household members with positive RDT test will be treated with single daily dose of DHAPPQ over three days in accordance with the national guideline for malaria cases management as follow: [5–8[Kg, DHA 20 mg/ PPQ 160 mg, one tablet/day, [8–11[Kg, DHA 20 mg/ PPQ 160 mg, 1 + 1/2 tablet /day, [11–17[Kg, DHA 40 mg/ PPQ 320 mg, one tablet/day, [17–25[Kg, DHA 40 mg/ PPQ 320 mg, 1 + 1/2 tablet /day and for [25–36[Kg, [36–60[Kg,, [60–80[Kg and ≥ 80 Kg, DHA 40 mg/ PPQ 320 mg, two, three, four and five tablets/day respectively. Enrolled children in both control and intervention arms will be followed for 24 months to fully cover two consecutive malaria transmission seasons, including two SMC cycles, and two dry seasons. However, the superiority will be measured over one season of intervention. The analysis will be repeated on year 2 to look at similar impact with potentially a difference in transmission. Then a pooled analysis of 2 years intervention will be conducted. Children will be actively followed-up with monthly visits during each of the two malaria transmission seasons (July–December). At each visit, physical examination will be performed and anthropometric parameters will be recorded, including weight, height, and Mid-Upper Arm Circumference (MUAC). Weight will be measured with SECA 874 scale (SECA company ltd., Germany). SHAKIR strips will be used for MUAC measurement. Blood smears will be collected by finger prick for hemoglobin (Hb) measurement, malaria Rapid Diagnostic Test (RDT), microscopy and additional drop of blood will also be spotted onto filter paper for later PCR analyses. In SMC+ screening and treatement of household members with standard RDT study arm, SD Bioline Malaria Ag P.f (HRP2/pLDH), (Standard Diagnostics, Inc., Korea) will be used. A HemoCue® 201+ will be used for photometric measurement of Hb in g/dL in the field. Thick and thin blood films will be stained with Giemsa 3% for 30 min and examined with light microscope Olympus CX23. Malaria slides will be double-read by two independent microscopists. In case of discrepencies a third reader will intervein and the arithmetic mean of the two nearest densities will be considered as final results. A smear will be declared negative if the examination of 100 thick-film fields does not reveal the presence of asexual parasites. The later PCR analyses will be the genotyping malaria-positive blood samples for amodiaquine resistance molecular markers in *pfcrt* and *pfmdr1*, sulfadoxine resistance marker in *pfdhps*, pyrimethamine resistance marker in *pfdhfr*, piperaquine resistance marker on Plasmepsin 2–3 and artemisinin resistance markers in the propeller domain of the Kelch 13 (K13) gene on malaria-positive samples. Samples will be genotyped using established protocols to detect molecular markers of antimalarial drug resistance. Briefly, DNA extracted from the dried blood spots will be used as the template for amplification by polymerase chain reaction (PCR). To detect nucleotide sequence polymorphisms, cleaned PCR products will be sent to a commercial service for Sanger sequencing. Single-nucleotide polymorphisms (SNPs) will be called by comparison with the reference sequences using validated bioinformatics workflows. Gene copy number amplifications will be detected using previously published protocols [20]. Children presenting any infection other than malaria will be diagnosed and treated appropriately according to national standard of care practices. After the malaria transmission season, the follow-up will be passive during the dry seasons (January–June). Parents / guardians of the enrolled children will be asked to contact the research team based at the peripheral health facilities of the study area in case their child is unwell. During these visits, children will be diagnosed and treated according to national standard of care practices. Nevertheless, all children will be actively seen on month 24 for a study end visit. Table 1 summarises the activites for the participant assessment and follow-up troughout the study (Table 1).

**Table 1 Tab1:** Participant assessment and follow-up troughout the study in the health district of Nanoro, Burkina Faso

Time point	Year 1							Year 2							
	M1	M2	M3	M4	M5	M6	M7-M12 Passive Follow-up	M13	M14	M15	M16	M17	M18	M19–23 Passive Follow-up	M24 Close out visit
Written Consent	X														
Inclusion/Exclusion criteria	X														
SMC rounds	X	X	X	X				X	X	X	X				
Confirmation of SMC Drug intake	X	X	X	X				X	X	X	X				
Roommates screening and treatment	X	X	X	X				X	X	X	X				
Physical examination and Anthropometric indicators	X	X	X	X	X	X		X	X	X	X	X	X		X
Blood sample for Hb, RDT, Microscopy and filter spots	X	X	X	X	X	X		X	X	X	X	X	X	X	X
Adverse Events	X	X	X	X	X			X	X	X	X	X			

In terms of confidentiality, all medical records of the participants as well as information displaying their names or address details will be kept confidential at the IRSS/CRUN. However, these identifying information could be seen in case of need by the ethics committee for health research, or the regulatory authority in Burkina Faso to ensure that the study is properly run in accordiance with national regulations.

